## Abstract

**Background:**

Well-being is multidimensional, complex, and dynamic in nature. It is an amalgam of physical and mental health, essential for disease prevention and the promotion of a healthy life.

**Objective:**

This study aims to explore the features that impact the well-being of individuals between 18 and 24 years of age in an Indian setting. It further aims to design, develop, and evaluate the usefulness and effectiveness of a web-based informatics platform or stand-alone intervention to enhance the well-being of individuals aged 18-24 years in an Indian setting.

**Methods:**

This study follows a mixed method approach to identify factors influencing the well-being of individuals in the age group of 18-24 years in an Indian setting. The college-going students in this age group from the states of Uttarakhand (urban settings of Dehradun) and Uttar Pradesh (urban settings of Meerut) will be enrolled. They will be randomly allocated to the control and intervention groups. The participants in the intervention group will have access to the web-based well-being platform.

**Results:**

This study will examine the factors that influence the well-being of individuals aged 18-24 years. It will also facilitate the design and development of the web-based platform or stand-alone intervention, which will enhance the well-being of individuals in the age group of 18-24 years in an Indian setting. Furthermore, the results of this study will help generate a well-being index for individuals to plan tailored interventions. The 60 in-depth interviews have been conducted as of September 30, 2022.

**Conclusions:**

The study will help understand the factors that influence the well-being of individuals. The findings of this study will help in the design and development of the web-based platform or stand-alone intervention to enhance the well-being of individuals in the age group of 18-24 years in an Indian setting.

**International Registered Report Identifier (IRRID):**

PRR1-10.2196/38632

## Introduction

### Background and Rationale

Well-being combines physical and mental health, essential for disease prevention and the promotion of a healthy life. It is complex and multidimensional in nature. Well-being consists of objective and subjective measures. The objective measures indicate the quality of life, whereas the subjective measures comprise spiritual, social, psychological, affective, and cognitive judgments [1].

Psychological well-being refers to the psychological aspect. It consists of hedonic well-being (eg, the feeling of happiness), evaluative well-being (eg, contentment from life), eudaimonic well-being (eg, self-actualization, to know the meaning of life), and the other aspects of feeling well (eg, optimism) [1].

Mental health is described as a condition of well-being in which the person understands his or her ability to manage the usual pressures of life, can work effectively and productively, and can also contribute to the community [2]. As per Global Health Estimates 2016, the leading cause of nonfatal disease is mental and substance use disorders [3]. In the United States in 2017, more than 46.6 million adults were reported to have mental illness in the previous year [4]. In the entire world, in 2017, mental health was the second leading cause of the burden of disease in terms of years lived with disability and the sixth main factor of disability-adjusted life-years, which is a substantial threat to health systems, especially in low- and middle-income countries. Mental health is considered a crucial factor around the world; therefore, it is included in health policies and Sustainable Development Goals [5].

One-fourth of the entire world population is between 10 and 24 years of age, and in South Asia and Africa, 1 in 3 people are young. Mental health problems range from 10% to 20% worldwide among children and young people [6]. A study in 27 countries assessed the pooled prevalence of global mental health problems to be 13.4% among children and young people [7]. Disruptive behavior was commonly observed among children and young people. It is estimated that, in young people aged 16-24 years, 1 in 4 has experienced a minimum of 1 mental health issue in the previous year. The literature has shown that young people worldwide are less aware of mental health. To promote the mental well-being of young individuals, there is a need to educate them, raise awareness, and develop interventions [8].

As per the Registrar General of India, 34.8% of India’s population is between 15 and 34 years of age, and it is projected to be 34.1% by 2021. In India, in 2017, the prevalence of mental disorders was 197.3 million, which comprised 45.7 million people with depressive disorders and 44.9 million with anxiety disorders [9]. This was due to an increase in issues like nutritional disorders, phubbing, sedentary lifestyles, social media addiction, and substance abuse in lower-income countries. A study has been carried out in rural India to find the effectiveness of delivering evidence-based psychological treatment for depression by training community health workers [10]. One of the prior studies has shown an association between unhealthy eating and anxiety, stress, and depression in university students [11].

Research has demonstrated the usefulness and effectiveness of web-based interventions in youth with mental health issues [8]. It has been seen that young people feel more comfortable gathering mental health information through the internet for sensitive and personal matters. Therefore, studies recommend that there be a need to promote personalized digital health interventions (DHIs). The intervention should have the ability to engage individuals by sending personalized messages, reminders, or alerts to increase motivation. Research has also shown that technology acceptance and user engagement can be increased by using pictures and interactive content [12].

The findings of one study depicted that, to promote well-being to a significant population level, there is a need for intervention and educational programs in all segments of society [13].

However, there is limited literature on DHIs to improve the well-being of youth in India [14,15].

### Study Objectives

The following are the proposed study objectives:

To examine factors that influence the well-being of individuals aged 18-24 years in an Indian settingTo design and develop the web-based platform or stand-alone intervention to enhance the well-being of individuals in the age group of 18-24 years in an Indian settingTo evaluate the usefulness and effectiveness of the proposed informatics-enabled decision aid platform to enhance the well-being of individuals aged 18-24 years in an Indian setting

## Methods

### Study Design and Population

A mixed methods approach will be adopted that uses both qualitative and quantitative data to identify factors influencing the well-being of individuals in the age group of 18-24 years in an Indian setting. In this study, 100 individuals will be enrolled each in the intervention and control group at Uttarakhand and Uttar Pradesh colleges.

We will design and develop the proposed platform using human-centered design principles. Individuals will be randomly allocated to an intervention group (access to the proposed well-being platform) and a control group (standard education). The standard educational material will be mailed to the participants in pdf format on the following topics:

Importance of physical activityRole of a balanced dietHow to cope with depression, anxiety, and stressSteps to lead a healthy life

### Study Setting

We will recruit college-going students aged 18-24 years from the states of Uttarakhand (urban Dehradun) and Uttar Pradesh (urban Meerut).

### Study Eligibility

The inclusion criteria are as follows: (1) individuals 18-24 years of age, (2) of any sex (male or female), and (3) willing to give informed written consent.

Participants will be excluded if they are younger than 18 years or older than 24 years, are not willing to give consent, or have any disability or chronic diseases. Figure 1 shows a schematic illustration of the methodology.

This study will follow a mixed methods pre- and postapproach for data collection using electronic data collection tools for qualitative and quantitative data from the study participants.

**Figure 1 figure1:**
[figure not shown]
Schematic illustration of the methodology.

### Achieving Objective 1

We will conduct 60 in-depth interviews by enrolling participants from Dehradun and Meerut. These interviews will be conducted through Zoom meetings, and the sessions will be recorded after having consent from the participants. Both quantitative and qualitative data will be gathered from the participants. In the interview, the participants will be asked questions to assess their awareness of well-being, the challenges they come across, how they deal with them, and the impact of COVID-19 on their well-being. Each interview will take around 15-45 minutes.

The data collected will help us examine the factors that influence the well-being of students in the age group of 18-24 years. Emphasis will also be placed on understanding individuals’ prior knowledge and attitude related to stress, unhealthy diet, and physical inactivity.

The data will be gathered on the following variables: sociodemographic profile, medical history, and anthropometric status; familiarity with technology; health behavior; Depression, Anxiety, and Stress Scale (DASS-21); General Self-Efficacy Scale; psychological well-being scales; global physical activity; and dietary diversity.

In addition, content analysis of the qualitative data will help generate critical themes on the well-being of students in the age group of 18-24 years in an Indian setting.

### Achieving Objective 2

We will use principles of a human-centered approach to design and develop a web-based informatics platform to improve the well-being of individuals in the age group of 18-24 years in an Indian setting.

The usability of the web-based informatics platform will be evaluated by individuals who will use it and will provide feedback. The literature has shown that a 10-item Likert scale questionnaire called System Usability Scale calculates the usability of websites, mobile devices, hardware, software, and other technological applications. Based on the feedback on usability evaluation, system modification can be done. Finally, the proposed web-based well-being platform will be implemented in a randomized controlled trial to evaluate its usefulness and effectiveness.

### Achieving Objective 3

We will perform a randomized controlled trial with 100 college-going students from Dehradun and Meerut each in the intervention and control group. So the total number of students enrolled will be 200. The students will be randomly allocated to either a control group or an intervention group. The students in the intervention group will have access to the web-based well-being platform. A study was carried out to evaluate the efficacy of a web- and mobile-based intervention on college-going students (n=150) [16].

The data will be collected on the following variables: sociodemographics, health behavior, health literacy, depression, stress, anxiety assessments, general efficacy, physical activity, and dietary pattern at baseline and a follow-up at 6 months.

### Study Groups

The study participants will be randomly allocated either to the intervention group or the control group.

#### Intervention Group

The participants in the intervention group will have access to the web-based well-being platform. It can be accessed from an Android smartphone or web-based platform. The proposed platform will have the following components: (1) screening component, (2) learning component, and (3) evaluation component.

Screening component: Variables recorded in the screening component include sociodemographics; health behavior (eg, physical activity levels and anthropometric assessments); health literacy; family history; familiarity with the use of technology; well-being scale; depression, stress, and anxiety assessments; and self-efficacy levels. In the screening component of the intervention, we will evaluate the health literacy level according to the education that will be given to the individual. Based on the data collected, a well-being index will be constructed to reflect on the variables attributing to the well-being of the youth. As the literature shows, well-being is dependent on various factors and is affected by the physical, social, and economic environment, life experience in every stage, family, poverty, and activity pattern [17,18].Learning component: Based on the well-being index generated for each individual, tailored messaging will be done using a series of culturally and contextually relevant messages. In this component, the individuals will get personalized feedback after interpreting the information gathered on all the parameters asked. In addition, they will receive weekly reminder messages to follow healthy behavior for their excellent well-being.Evaluation component: We will assess the usefulness and acceptance of the system using the system usability scale and monitor the usage. In addition, we will determine youth well-being using the well-being scale at baseline and a follow-up at 6 months.

### Informed Consent

The ethics committee of the university has approved the informed consent form. The research team will obtain the consent from all the individuals participating in the study. The research team will also explain them the analysis, duration, and need of the study. Individuals who are willing to participate will be asked to sign the consent form, and a copy of the consent form with study details will be given to them. The study is on college-going students, so everyone will be able to read and write. The research team is aware of both English and Hindi language, so they will be able to understand the response. The data captured will be stored safely and protected. The confidentiality of data will be maintained. The participants will be allowed to withdraw from the ongoing study anytime by giving reasons to withdraw. All the data gathered, including those from the participants who will withdraw, will be reported for the final analysis. No monetary compensation will be given to the participants enrolled in the study. The voluntary participation and time of the participants will be respected.

### Data Collection, Data Entry, and Quality Assurance

The data will be collected and entered by following standard techniques and protocols. Complete confidentiality of the information obtained from the study participants will be ensured. Frequent backups will retain all the data gathered, and all computers and specific data files will be password protected and kept in a locked file cabinet.

### Variable Assessment

#### Sociodemographic and Family History

The questionnaire included questions regarding the demographic factors of the respondents, like age, sex, family history, educational status, occupation, and income levels.

#### Health Behavior

Four crucial behavioral risk factors will be collected: tobacco consumption, alcohol consumption, impact of COVID-19, and sleep duration.

#### Familiarity With Technology

Individual assessment will include access to the type of smartphone, familiarity with the use of the internet, and knowledge of texting.

#### Anthropometric Measurements

Variables assessed include duration of diabetes, recent blood sugar report, type of medication, and height and weight measures that would help calculate BMI.

The measures in Textbox 1 will be administered.

Measures to be used.
**Sociodemographic and family history**
Age; sex; educational status; religion; income, if any; parents’ occupation
**Health literacy**
Rapid Estimate of Adult Literacy in Medicine scale
**Familiarity with technology**
Access to the smartphone and internet and knowledge of texting
**Health behavior**
Information on smoking, alcohol, physical activity, and substance abuse disorders
**Well-being scale**
Ryff scale
**Depression, stress, and anxiety assessments**
Depression, Anxiety, and Stress Scale
**Self-efficacy**
General Self-Efficacy Scale
**Dietary diversity**
Food and Nutrition Technical Assistance Diet Diversity
**Anthropometric measurements**
Height, weight, BMI
**Physical activity**
Global Physical Activity Questionnaire
**System usability**
System Usability Scale

### Data Security and Privacy

The data security will be done through regular backups, and all computers and specific data files will be password protected and kept in a locked file cabinet. In addition, the computers in which data is stored will be password protected and safely stored for 3 years after the completion of the study.

### Outcomes

The well-being index generated from this study can be used in other geographic regions for a similar population. If the youth of a nation is healthy, it will lead to the country’s growth.

The primary outcome of the study will be development of the student well-being index among urban settings. This will also facilitate the understanding of the various factors that affect the student well-being.

The secondary outcome of this study will further help us to understand the relationship between sociodemographic factors with dietary diversity, physical activity, depression, stress, and anxiety among college-going students.

A cross-sectional study was conducted, and the results showed significant associations between physical activity levels and sleep quality with mental health. The mental health issues are the same in both male and female college students [19].

The outcomes will be assessed by using the following tools.

#### Health Literacy

Health literacy is defined as the cognitive and social skills that determine the motivation and ability of individuals to gain access to, understand, and use information in ways that promote and maintain good health [20]. Conversely, low literacy can create misunderstanding of the environment and impact health outcomes [21].

Health literacy requires acquiring information, processing it, and then understanding the data to develop the reasoning required to make the decision. Many studies have shown that literacy level is related to cost and health characteristics like knowledge, health status, and health facilities. However, little work has been done on the health literacy of adolescents and young adults. The literature also shows the association between poor health literacy and adverse health outcomes such as smoking and obesity [22].

The Rapid Estimate of Adult Literacy in Medicine is one of the most accepted tests to assess health literacy. This test is performed by seeing the patient’s potential to pronounce 66 words, including lay terms for parts of the body, illnesses, and common medical words. It is a quick tool that can be administered in less than 2 minutes. As a result, it is one of the most popular tools for assessing health literacy levels. The scoring is divided into 2 groups: 0-44=low health literacy and 45-66=higher health literacy.

#### Well-being Scale

The Ryff scale is a 42-item scale that measures 6 dimensions of well-being and happiness: environmental mastery, self-acceptance, purpose in life, positive relations with others, autonomy, and personal growth [20].

#### Depression, Anxiety, and Stress Scale

A randomized control trial was conducted on young adults to reduce the symptoms of depression with a brief diet intervention. In this study, the DASS-21 tool will be used to assess the symptoms of depression [23].

This scale evaluates depression, anxiety, and stress associated with a negative emotional situation. It is a 42-item self-report questionnaire that has been concise to a scale of 21. It measures on a 0-3 pointing scale, where 0 is for “did not apply to me” and 3 stands for “applicable to me or majority of the time.”

#### Dietary Diversity

In lower-income countries, dietary diversity tools are used to study dietary adequacy. Dietary diversity is a significant problem among poor people as they usually consume starchy staples with or without limited consumption of animal products, fruits, and vegetables [24].

The Food and Nutrition Technical Assistance Diet Diversity score will be computed based on the information obtained regarding consuming several food items within each food group.

#### General Self-Efficacy Scale

It is a 10-item tool validated in Asia [7]. It can also be applied to diverse cultural backgrounds and positively correlated with depression, anxiety, and optimism. To calculate the total score, the total of all items is considered. The total score ranges between 10 and 40, with a higher score indicating more self-efficacy. It is universally accepted and considered an adequate scale to measure self-reported self-efficacy. A relation has been seen in general self-efficacy and social cognitive variables, health behavior, and well-being [25,26].

#### International Physical Activity Questionnaire

The International Physical Activity Questionnaire is considered a validated tool to monitor physical activity among youth and older adults in diverse settings [27].

The participants will complete the questionnaire so that their physical activity can be assessed. The total time spent in physical activity for recreation, occupation, household work, and transportation in the past 7 days will be calculated. The total weekly physical activity (metabolic equivalents of task [MET-hour/week]) will be calculated as the weighted sum of the reported time spent at each intensity using an MET value specific to each category.

#### Data Analysis Plan

The data gathered at baseline will include sociodemographics, KAP (knowledge, attitude, and practice), diet assessment, physical activity, health literacy, social media, and familiarity with technology. Baseline and follow-up data collected will be statistically analyzed.

For continuous and categorical variables, means and SDs and frequencies, respectively, will be calculated. Finally, cross-tabulation of the data from the intervention group against outcome variables will be done to calculate the direction and degree of association in this initial stage. The analysis will be done using SAS v9.3 (SAS Institute), and the results will be reported at 95% CIs and *P*=.049.

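### The only association analysis in the plan names the intervention group alone, and no comparison with the control group is stated, so as written it cannot estimate the platform's effect

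*Protocol article*

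**What the plan says.** The third aim under Study Objectives is to evaluate whether the platform is useful and effective. Achieving Objective 3 gives the design: "We will perform a randomized controlled trial with 100 college-going students from Dehradun and Meerut each in the intervention and control group", with the total in the next sentence, "So the total number of students enrolled will be 200", and the allocation after that, "The students will be randomly allocated to either a control group or an intervention group". Study Design and Population gives the control group standard education, sent as pdf material. Outcomes are collected at baseline and 6 months (Achieving Objective 3; Intervention Group, evaluation component).

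The Data Analysis Plan has three statements on method:

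- a general one: "Baseline and follow-up data collected will be statistically analyzed";
- a descriptive one: "For continuous and categorical variables, means and SDs and frequencies, respectively, will be calculated";
- the only one about association, introduced as the last step: "cross-tabulation of the data from the intervention group against outcome variables will be done to calculate the direction and degree of association", which the sentence places at an initial stage.

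The control group is not mentioned in that section.

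**The concern.** A randomised trial estimates an effect by contrasting the groups as allocated. The stated analysis names one group. Everyone in it has platform access, so the exposure is constant and nothing cross-tabulated within that group can measure what access does. The stated method therefore fits neither the randomised design nor the effectiveness objective.

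The practical risk is what fills the gap. With baseline and 6-month data and an analysis that names one arm, the likely substitute is a change from baseline among platform users. Any shift that would have happened anyway over six months, regression to the mean and the effect of repeating the questionnaires would then be mixed with the platform's effect. The control group exists to remove these.

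**Working it through.** **Step 1. Design against analysis.**

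| Element | What the article states |
|---|---|
| Question | Usefulness and effectiveness of the platform (Study Objectives) |
| Groups | Platform versus standard education, randomised, 100 + 100 = 200 (Study Design and Population; Achieving Objective 3) |
| Time points | Baseline and 6 months (Achieving Objective 3; Intervention Group) |
| Descriptive analysis | Means, SDs, frequencies; not said to be by group (Data Analysis Plan) |
| Association analysis | Intervention-group data against outcomes (Data Analysis Plan) |
| Intervention versus control | Not stated in any section |

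The total of 200 is consistent. The figure of 100 per arm cannot be reproduced, because the article gives no effect size, SD or power.

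**Step 2. What a one-arm reading could cost (illustration).** From the article: n = 100 in the intervention group. Assumed: no platform effect, a drift s shared by all participants, pre-post correlation r, outcome SD of 1, full retention, two-sided 0.05, normal approximation.

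SE of the mean change = sqrt(2(1 − r)/100). Probability of a significant result = 1 − Φ(1.96 − s/SE) + Φ(−1.96 − s/SE).

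Example, r = 0.5 and s = 0.2: SE = sqrt(1.0/100) = 0.100, s/SE = 2.00, probability = 1 − Φ(−0.04) + Φ(−3.96) = 0.516.

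| r | SE | s = 0.1 | s = 0.2 | s = 0.3 |
|---|---|---|---|---|
| 0.3 | 0.118 | 0.135 | 0.394 | 0.718 |
| 0.5 | 0.100 | 0.170 | 0.516 | 0.851 |
| 0.7 | 0.077 | 0.252 | 0.733 | 0.972 |

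In the between-arm comparison the shared drift cancels, and the error rate stays at 0.05.

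**Step 3. What the between-arm comparison delivers.** With 100 per arm, two-sided 0.05 and 80% power, the detectable difference on follow-up scores alone is (1.960 + 0.842) × sqrt(2/100) = 0.396 SD. Adjusting for baseline multiplies this by sqrt(1 − r²):

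| r | Residual variance, 1 − r² | Detectable difference (SD) | Power at an assumed 0.3 SD effect |
|---|---|---|---|
| unadjusted | 1.00 | 0.396 | 56.4% |
| 0.3 | 0.91 | 0.378 | 60.4% |
| 0.5 | 0.75 | 0.343 | 68.8% |
| 0.7 | 0.51 | 0.283 | 84.4% |

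At the article's threshold of .049 the unadjusted values are 0.397 SD and 56.1%, so the choice of 0.05 here changes nothing of substance.

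**The case against.** The strongest reply is that the sentence is a slip. Several sections describe a randomised trial with a control arm, and the authors may have meant allocation by outcome. The sentence itself limits the calculation to a "degree of association in this initial stage", the plan says in general terms that baseline and follow-up data will be analysed, and the Informed Consent section refers to a final analysis of all data gathered. A journal article also leaves model detail to fuller documents that are not at hand.

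Much of this stands, and it rules out several stronger readings:

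- A reader might infer that the control group will never be compared. The article does not say so. It neither confines the analysis to one arm nor excludes the controls.
- A reader might infer that a one-arm before-after test is planned. The Study Eligibility section says "This study will follow a mixed methods pre- and postapproach for data collection", which concerns when data are gathered. A controlled trial with two visits fits that description too. The percentages in step 2 of the working therefore belong to a possible misuse and not to a stated test.
- A reader might infer that continuous scores will be split, for instance at the median, with a loss of information. No such split is stated. The only stated cut is for health literacy (0-44 versus 45-66), and continuous variables are to be summarised by means and SDs.
- A reader might count the absence of baseline adjustment as a second error. It is neither planned nor excluded, and the choice of covariates is commonly left to the statistical analysis plan.

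The reply does not rescue the sentence. It states a method, names one arm and says what will be calculated. No later stage is described, and neither the general statement nor the reference to a final analysis names a contrast. This is an analysis stated badly, which is different from detail left out. A fuller plan that followed the wording would carry the fault forward.

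**Conclusion.** The point holds in this form: the one association analysis stated names the intervention group alone, no between-group comparison is stated, and the analysis as written cannot answer the effectiveness objective. This rests on the text and needs no assumed figure.

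The size can only be illustrated. The false-positive range depends on a one-arm reading that the text does not fix, and on an assumed drift. At 0.1 SD in place of 0.2 SD it falls to about 14% to 25%. The gain from baseline adjustment is small at a correlation of 0.3 and large at 0.7, and the article gives no value. That gain supports the choice of remedy and is not a separate defect.

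The sentence must be corrected before analysis, because an effectiveness claim cannot rest on it.

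**What to change.** Replace the cross-tabulation sentence in the Data Analysis Plan, and carry the same text into any statistical analysis plan, with wording such as:

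> All randomised participants are analysed in the group to which they were allocated. Each continuous 6-month score is compared between the intervention and control groups by ANCOVA with the baseline score as covariate, and the adjusted mean difference is reported with its 95% confidence interval. Cross-tabulations are descriptive and are shown for both groups.

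City (Dehradun or Meerut) may be added as a covariate; the point does not depend on it. The essential element is the between-arm contrast at 6 months. ANCOVA is the recommended way to state it, since the baseline scores are already being collected.

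The cost is a change of wording. No new data, visits or participants are needed, and the model is standard in the SAS software already named.

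### Cross-tabulation is the only association method the article names, but most outcomes are numeric scores with no categories defined; analyse them uncut

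*Protocol article*

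**What the plan says.** The Data Analysis Plan first gives descriptive summaries: "For continuous and categorical variables, means and SDs and frequencies, respectively, will be calculated". It then names its one method for association: "cross-tabulation of the data from the intervention group against outcome variables will be done to calculate the direction and degree of association". The sentence goes on to describe this as an initial stage. The next sentence says that "the results will be reported at 95% CIs", with a P value of .049. No other association method or between-group comparison is named in the article.

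The secondary outcome, under Outcomes, is the "relationship between sociodemographic factors with dietary diversity, physical activity, depression, stress, and anxiety among college-going students". Objective 3 is a randomised comparison with "100 college-going students from Dehradun and Meerut each in the intervention and control group", measured at baseline and at 6 months.

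The tools are described mainly as scores:
- **Self-efficacy:** "The total score ranges between 10 and 40, with a higher score indicating more self-efficacy".
- **Physical activity:** "The total weekly physical activity (metabolic equivalents of task [MET-hour/week]) will be calculated as the weighted sum" of time at each intensity.
- **DASS-21:** items scored 0 to 3.
- **Ryff scale:** 42 items in six dimensions.
- **Dietary diversity:** a computed score.
- **Health literacy:** the only tool with a cut, 0-44 (low) v 45-66 (higher).

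**The concern.** A useful cross-tabulation needs categories. For a sum score or for MET-hours per week, someone must first decide where one category ends and the next begins, and for most of these scores the article does not say. The plan also sits awkwardly with itself: it summarises continuous variables by mean and SD, then gives the job of measuring association to a method for categorical data.

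Precision and interpretation are at stake. Grouping a score discards the differences within each group, so a trial of fixed size can detect less. The result is a difference in proportions, not a difference in scale units. The Limitations section already concedes that the sample is small, so there is little precision to spare.

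**Working it through.** The article gives no power, effect size or SD behind its sample size, and no figure for information loss, so there is no plan figure to reproduce. The check asks what grouping would cost.

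**Inputs from the article.** 100 per arm ("So the total number of students enrolled will be 200"), 95% CIs, and score outcomes without categories.

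**Assumptions.** Normally distributed scores with equal SDs; a true difference of 0.3 to 0.5 SD; a two-sided 5% test. Using .049 instead changes power by less than half a percentage point.

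**Step 1: information kept after grouping.** For a normal score, the share kept is the sum over categories of (difference in normal density at the two category limits)² ÷ (category probability). For one cut at the median, the density there is 1/√(2π), so the share is 2 × (1/(2π)) ÷ 0.5 = 2/π = 0.637.

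| Grouping | Share kept | Loss |
|---|---|---|
| Two groups, 50/50 | 0.637 | 36% |
| Two groups, 30/70 | 0.576 | 42% |
| Two groups, 20/80 | 0.490 | 51% |
| Two groups, 10/90 | 0.342 | 66% |
| Thirds | 0.793 | 21% |
| Quarters | 0.861 | 14% |
| Fifths | 0.897 | 10% |

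At a median cut, 200 students carry the information of 200 × 0.637 = 127.

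**Step 2: power at 100 per group, 0.4 SD.**
- Uncut score: Φ(0.4 × √(100/2) − 1.96) = Φ(0.868) = 0.807.
- Median cut: the proportions above the cut are Φ(−0.2) = 0.421 and Φ(0.2) = 0.579, a difference of 0.1585. The standard error is 0.0707 under no difference and 0.0698 under the alternative. Power = Φ((0.1585 − 1.96 × 0.0707)/0.0698) = 0.612.

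| Assumed difference | Uncut score | Median cut |
|---|---|---|
| 0.3 SD | 56% | 39% |
| 0.4 SD | 81% | 61% |
| 0.5 SD | 94% | 80% |

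If only 80 per arm were analysed (an assumption), the 0.4 SD row would read 72% and 52%.

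**Step 3: simulation at 0.4 SD.** Power was about 80% on the score, 64-66% after a cut at the pooled median with an uncorrected chi-square test, and 50-51% after a cut at the top 20%. The 66% is slightly flattering, because that test rejected in about 6.7% of runs with no true difference. With a continuity correction the median-cut figure was 55%. The analytic 61% lies between.

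**Step 4: the same loss as sample size.** The difference detectable with 80% power at 100 per arm is (1.960 + 0.842) × √(2/100) = 0.396 SD. After a median cut, detecting 0.396 SD with 80% power takes 158 per arm.

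**The case against.** The cross-tabulation sentence describes an initial stage, and the sentences around it plan means, SDs and 95% CIs. None of these requires cutting a score, so a comparison of means is not excluded. This is also a condensed article: category bands and fuller models may sit in a full protocol or analysis plan that is not shown. All of this stands, and it limits the point to a mismatch between the method written and the outcomes it is written for. It does not remove the mismatch. No later stage of association analysis is described, the timeline in Table 1 shows a single analysis period (months 15-17) followed by writing, and the summaries are descriptive.

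Three stronger readings are tempting, and the article does not support them.

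- **That scores must be cut after the data are seen, with inflated false positives.** Reporting the best of 3, 5 or 9 cuts would raise a nominal 5% error to about 11%, 18% or 24% in simulation. But no such search is proposed, and the one cut the article gives, for health literacy, is fixed in advance.
- **That the secondary outcome will be estimated by one-factor tables and so stay confounded.** The cross-tabulation sentence concerns intervention-group data against outcomes. It does not mention sociodemographic factors, and the article ties no specific method to the secondary outcome.
- **That a third of the information will be lost.** That figure belongs to a single cut near the median of a normal score. Ordered groups lose less, and cuts further from the median lose more.

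**Conclusion.** The point holds as a mismatch of method and outcome type. Cross-tabulation is the only association method named, and for most outcomes it could be used only after grouping scores for which the article defines no groups. Whether grouping will be done, and where, is not stated, so the loss is conditional: about 36% of the information for one median cut, with a range of about 10% (fifths) to 66% (a 10/90 cut). At an assumed 0.4 SD and 100 per group, a median cut lowers power from about 80% to roughly 61-66%.

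These sizes rest on normal scores and assumed effects; the article gives no distribution for any score. The 100 per group is the size of the trial arms. Sociodemographic comparisons, such as by sex or city, may be less balanced, with lower power both before and after grouping.

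**What to change.** State in the Data Analysis Plan that scale scores are analysed uncut.

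- **Randomised comparison (Objective 3):** compare the six-month scores between arms by linear regression adjusted for the baseline score. Report the adjusted mean difference with its 95% CI.
- **Secondary outcome:** regress each baseline score (DASS-21 depression, anxiety and stress; dietary diversity; MET-hours per week) on the sociodemographic factors together, for example age, sex, education, income, religion, parents' occupation and city. Report adjusted mean differences with 95% CIs.
- **MET-hours:** these may be skewed, so allow for a transformation or robust standard errors.
- **Cross-tabulation:** keep it for truly categorical variables such as tobacco and alcohol use, and for score categories fixed in advance, as is already done for health literacy.

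The cost is wording and a little more analysis, with no additional participants or instruments. The article reports only the 60 interviews as done and describes the trial data as still to be collected. One detail to confirm in the same edit is that the Ryff scale is taken in both arms, because its six-month reading is mentioned only under the platform's evaluation component.
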